### 7.4. Risk Analysis

See section 1.4 for the risk-benefit assessment, and section 9.7.1.5 for the continuous risk-benefit assessment.

For Publication Purposes

## 8. Statistical methods

### 8.1. Analysis populations

Primary analysis will be performed on in the Modified Intention-To-Treat population. For both the Per-Protocol population and As-Treated population only the Primary endpoint, and its individual components, will be tabulated (no formal testing will be applied).

#### 8.1.1. Modified intention-to-treat (mITT) population

The modified intention-to-treat analysis population will include all randomized participants who underwent the PCI procedure.

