IVUS has been compared to fractional flow reserve (FFR) in three groups of patients with inconsistent results. Jasti *et al* initially reported that an IVUS MLA of  $5.9 \text{ mm}^2$  (sensitivity of 93% and specificity of 95%) and an MLD of < 2.8 mm (sensitivity of 93% and specificity of 98%, respectively) for determining an FFR of < 0.75. Subsequently, Kang *et al* reported that the IVUS MLA that best predicted FFR < 0.80 was <  $4.8 \text{ mm}^2$  (89% sensitivity, 83% specificity, area under the curve [AUC] 0.90,  $p < 0.001$ ). In addition, the cutoff value of plaque burden to predict FFR < 0.80 was  $\geq 72\%$  (sensitivity 73%, specificity 79%, AUC 0.79,  $p < 0.001$ ). Of note, the FFR was significantly lower in 18 lesions with plaque rupture vs 37 lesions without plaque rupture ( $0.76 \pm 0.09$  vs  $0.82 \pm 0.09$ ,  $p = 0.018$ ). In a follow-up study done by Park *et al*, in an expanded group of 112 patients, the independent factors of an FFR of  $\leq 0.80$  were plaque rupture (odds ratio [OR] 4.47,  $p = 0.014$ ), body mass index (OR 1.19,  $p = 0.05$ ), patient age (OR 0.95,  $p = 0.031$ ), and IVUS MLA (OR 0.37,  $p < 0.001$ ). The optimal IVUS MLA cut-off for an FFR of  $\leq 0.80$  was  $4.5 \text{ mm}^2$  (77% sensitivity, 82% specificity, AUC 0.83,  $p < 0.001$ ) with an optimal IVUS plaque burden cutoff of 77% (70% sensitivity, 82% specificity, and AUC: 0.80). The most plausible explanation for the differences between the

minimal MLA in the studies by Jasti, Kang, and Park appeared to be the ethnicity of the patient populations as a comparison of white North American vs Asian patients showed a smaller MLA in Asian patients ( $5.2 \pm 1.8 \text{ mm}^2$  vs.  $6.2 \pm 1.4 \text{ mm}^2$ ,  $p < 0.0001$ ).

Notably, given the unique prognostic implications of LM disease the European Bifurcation Club (EBC) recommended using a threshold cutoff of MLA  $\leq 6 \text{ mm}^2$  to indicate an LMCA that should be treated with revascularization.

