## 3. Study Design

The OPTIMAL study is a randomized, controlled, multicentre, international, post-marketing strategy study. The hypothesis is that an IVUS-guided approach is superior to a qualitative angio-guided approach in the setting of left-main PCI.

A total of 800 patients will be randomized in a 1:1 fashion to IVUS-guided PCI versus qualitative angio-guided PCI. Patients will be screened for inclusion/exclusion criteria after the indication for PCI of the LM. After confirmation of the in-and exclusion criteria and signing of informed consent form, participants are enrolled, followed by randomization to IVUS-guided or qualitative angio-guided PCI with Synergy or Synergy Megatron stent implantation. Both the participants and investigators are not blinded for the procedure. Participants are followed up for 2 years after the index procedure, with a phone call at 1 month and clinical onsite visits or phone calls at 1 and 2 years. Up to 30 sites in Europe will participate in this study. The total study duration from first patient in to last patient out is expected to be approximately 4 years.

The OPTIMAL trial is performed in accordance with the Declaration of Helsinki, Good Clinical Practice (GCP), ISO 14155:2020, EC requirements and country specific regulations.

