### 5.3. Enrollment & randomization

Enrollment will occur after all inclusion criteria are met and no exclusion criteria are present.

All patients participating in this clinical trial will provide informed consent prior to enrollment. Patients who were unable to provide informed consent prior to the PCI procedure cannot be enrolled.

Once patient signs ICF (or provides an oral consent with a witness, in case of ad-hoc PCIs), the Investigator or designee registers the participant in the electronic data capturing (EDC) system. The Investigator or designee is prepared to provide participant-related details, including IC date, the year of birth, age and sex. Based on this information, the system assigns a unique participant identification number.

After enrollment and after final eligibility is established, the participant is randomized at a 1:1 ratio to IVUS-guided PCI or qualitative angio-guided PCI using the randomization module of the EDC. Stratification by site is performed to ensure balance across potential local differences in treatment practices.

If after informed consent, final eligibility cannot be established, the patient is considered a screening failure and is not randomized. All randomized patients are followed-up and included in the Full Analysis Set population.

It is strongly recommended that the PCI procedure is scheduled within 24 hours after informed consent, or within 72 hours for stable patients. If a consented patient is randomized and treated **after** 72 hours, reasons must be documented in the EDC. A consented patient that is not randomized within 4 weeks, will no longer be eligible and will be considered a screening failure.

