#### 8.1.2. Per Protocol (PP) population

The per-protocol population will include all randomized participants in whom PCI was performed according to their randomized arm, thus excluding cross-overs, and participants of which the LM was not treated with PCI.

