#### 8.1.3. As treated (AT) population

The As Treated population will include all randomized participants who underwent the PCI procedure, participants will be reported according to the actual treatment received.

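### The primary analysis keeps only randomised patients who went on to PCI; the Full Analysis Set of all randomised patients promised in Section 5.3 is never defined or analysed.

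*Protocol*

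**What the plan says.** The Protocol outline and Section 8.1 agree on the primary population: "Primary analysis will be performed on in the Modified Intention-To-Treat population". Section 8.1.1 defines it: "The modified intention-to-treat analysis population will include all randomized participants who underwent the PCI procedure".

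Randomisation comes before PCI (outline; Sections 3 and 5.3). Section 5.3 strongly recommends PCI within 24 hours of consent, or 72 hours in stable patients, and accepts later treatment if the reason is recorded. Allocation is open: "Both the participants and investigators are not blinded for the procedure" (Section 3).

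Section 5.3 also states: "All randomized patients are followed-up and included in the Full Analysis Set population". Section 8.1 contains no such set. Its other two populations are per-protocol ("The per-protocol population will include all randomized participants in whom PCI was performed according to their randomized arm", without cross-overs and patients whose left main was not treated by PCI) and as-treated ("The As Treated population will include all randomized participants who underwent the PCI procedure"). For these two, only the primary endpoint and its components are tabulated, without a formal test.

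Follow-up is timed from the index procedure (Section 3; Schedule of Assessments). Serious adverse events are collected from consent (Section 7.3). Section 8.2.1 gives no time origin for the Kaplan-Meier analysis.

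**The concern.** The hypothesis in Sections 2.1 and 3 concerns a strategy. Randomisation protects the comparison of strategies only while everyone allocated stays in it. Here a patient who dies waiting, is sent to surgery, is deferred or withdraws before PCI leaves the primary analysis, and the people making or influencing that decision know the allocation. If the number or the risk of such patients differs by arm, the two analysed groups are no longer the randomised groups.

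The protocol expects that some randomised patients will not have left main PCI, because Section 8.1.2 provides for them. Section 8.1.1 does not say whether the PCI it requires must be of the left main. A patient whose left main was deferred could therefore stay in or drop out depending on whether another vessel was stented.

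There is also no fallback. PP and AT carry the same condition, and the one set that would restore the randomised comparison exists in name only.

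**Working it through.** **Side by side.**

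| Set | Where | Requires PCI? | Planned use |
|---|---|---|---|
| Full Analysis Set | 5.3 | No | None stated |
| mITT | 8.1.1 | Yes | Primary, confirmatory |
| Per-protocol | 8.1.2 | Yes | Tabulated |
| As-treated | 8.1.3 | Yes | Tabulated |

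**The plan's own figure (Section 8.3).** Inputs: 17% against 26%, cross-over 3% from IVUS and 4% from angiography, two-sided 0.05, 80% power.

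- IVUS arm: 0.97 × 17% + 0.03 × 26% = 17.27%.
- Angiography arm: 0.96 × 26% + 0.04 × 17% = 25.64%.
- Risk difference: -8.37 points.
- Total N for a two-proportion Z test: 754 without and 800 with continuity correction. The stated 789 lies between them and gives 81.8% power without the correction. Power at 400 per arm is 82.3%.

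**Possible shift in the risk difference.** The protocol gives no count or event rate for patients without PCI, so these are assumptions. Take 400 per arm. Expected events among all randomised are 400 × 0.1727 = 69.08 and 400 × 0.2564 = 102.56. In the first three rows, 12 IVUS patients and 4 angiography patients (event risk 25%) have no PCI, and the angiography term is (102.56 - 1)/396 = 25.65%.

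| Risk in excluded IVUS patients | IVUS arm in mITT | Risk difference | Shift (points) |
|---|---|---|---|
| 50% (assumed) | (69.08 - 6)/388 = 16.26% | -9.39 | 1.0 favouring IVUS |
| 37.5% | (69.08 - 4.5)/388 = 16.64% | -9.00 | 0.6 favouring IVUS |
| 12.7% | (69.08 - 1.52)/388 = 17.41% | -8.24 | 0.1 against IVUS |
| 8 excluded per arm, 50% vs 25% | (69.08 - 4)/392 = 16.60%; angiography (102.56 - 2)/392 = 25.65% | -9.05 | 0.7 favouring IVUS |

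The 12.7% is 100% minus the 87.3% two-year event-free survival of deferred patients in the left main registry described in the Introduction. The 37.5% is 100% minus the 62.5% for 16 unrevascularised patients with smaller lumen areas in the same registry; no follow-up time is attached to that figure. Neither registry endpoint is stated to match the trial's composite.

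**No true difference.** Let both arms have 26% and drop a fraction u of the IVUS arm only, with event risk p. The analysed IVUS rate is (0.26 - u·p)/(1 - u). With p from 50% to 100%:

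- u = 1%: shift 0.2 to 0.75 points; two-sided type I error 5.1 to 5.7%.
- u = 2%: shift 0.5 to 1.5 points; 5.3 to 7.8%.
- u = 5%: shift 1.3 to 3.9 points; 6.9 to 24.7%.

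**Power cost of keeping everyone.** Suppose a fraction u per arm has no PCI, with a common event rate of 17 to 40%. Each arm's rate is then (1 - u) × its diluted rate + u × the common rate. At 400 per arm:

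- u = 1%: 81.6 to 81.3%, against 82.0% for mITT with the same patients dropped.
- u = 3%: 80.2 to 79.3%, against 81.2%.

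With 6% attrition as well (376 per arm), power is 79.2 to 76.7% over the same range, against 80.0% if every patient has PCI.

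**The case against.** The strongest reply is that few patients will be affected and the arm-specific route is mostly closed beforehand. Exclusion criterion 3 and Section 5.5.1 remove, before randomisation, patients who need IVUS to judge lesion severity. Inclusion criterion 3 requires PCI to be judged appropriate and feasible. PCI is recommended soon after consent. All of this stands, and it is why the effect is probably small.

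Several stronger readings are tempting but are not supported:

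- A reader might infer that only IVUS-arm patients can be imaged before PCI and then deferred. Section 5.5.1 disallows pre-PCI IVUS in the angiography arm but provides for it as a cross-over, and Section 8.3 assumes 4% such cross-overs. The Introduction's lumen-area threshold "to indicate an LMCA that should be treated with revascularization" reports a consensus recommendation. It is not a trial rule for deferral after randomisation.
- A reader might infer that events between randomisation and PCI are not counted. No section says so. Serious adverse events are collected from consent; what is missing is a time origin.
- A reader might infer that the protocol names two different primary populations. It does not. The outline and Section 8.1 agree on mITT, and Section 5.3 never calls the Full Analysis Set primary. The flaw is a promised set with no definition and no analysis.
- A reader might take the 1.0-point shift (1.02/8.37, about 12%) as the expected bias. It needs a 3:1 imbalance and risks of 50% against 25%, none of which the protocol supports. The 24.7% type I error needs 5% lost from one arm only, all with events.

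The objection that an all-randomised analysis needs more than rewording also stands. Visits are timed from PCI, and it is unstated whether a first revascularisation in an untreated patient counts as a repeat one. The target lesion, too, is defined by what was treated at the index or staged procedure.

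**Conclusion.** The point holds as a design weakness with an internal gap, and it should be fixed. The sole confirmatory test is conditional on an event after open-label allocation, and no analysis named in the protocol retains all randomised patients. Exclusion could differ by arm, but the documents do not show that it will.

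The direction is not predictable: high-risk exclusions from the IVUS arm would flatter IVUS, and low-risk deferrals would work slightly against it. Over the scenarios with 12 and 4 exclusions, the range is about 0.1 point against IVUS to about 1 point in its favour on -8.4 points. This rests entirely on assumed counts and risks. If everyone randomised has PCI, mITT and the all-randomised set contain the same patients and there is no exclusion bias. An unseen SAP may define the Full Analysis Set, but the protocol itself fixes mITT as primary.

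**What to change.** 1. In Section 8.1, define the Full Analysis Set as all randomised participants, analysed as randomised, with time zero at randomisation. Make it the primary population and align the Statistical analysis row of the outline.
2. Keep mITT as a sensitivity analysis, and state whether its PCI condition means left main PCI or any PCI. Leave PP and AT as tabulations.
3. State how the follow-up schedule, and the repeat-revascularisation component of the primary endpoint (Section 6), apply to a participant who never had index PCI. State the same for the endpoints that depend on a target lesion.
4. Report participants without PCI by arm, with reasons and timing.

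Cost: Sections 5.3 and 5.15 already commit to following these patients, so the extra work is mainly protocol text and the rules in item 3. Untreated patients dilute the effect slightly. If 1 to 3% per arm have no PCI, power at 400 per arm falls from 82.3% to between 81.6% and 79.3%, about 1 to 3 points. Part of that loss would occur under mITT anyway, because the same patients would be dropped.

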#### 8.1.2. Per Protocol (PP) population

The per-protocol population will include all randomized participants in whom PCI was performed according to their randomized arm, thus excluding cross-overs, and participants of which the LM was not treated with PCI.

#### 8.1.3. As treated (AT) population

The As Treated population will include all randomized participants who underwent the PCI procedure, participants will be reported according to the actual treatment received.

### 8.2. Statistical analysis

The statistical analysis of the primary endpoint is confirmatory. The statistical analysis of the secondary endpoints is exploratory. This section indicates how the primary endpoint and the clinical secondary event points are analyzed.

#### 8.2.1. Time dependent endpoints

Analysis of clinical primary and secondary endpoints will be performed. Two types of time-to-event, Kaplan-Meier (KM), analyses are performed. When the KM-curves for the IVUS guidance arm and the Angio Guidance arm are compared the regular KM-analysis is performed to compare the survival distributions of the two arms, using the log-rank test. This method is non-parametric.

Additionally the KM-estimates for the two arms at a single fixed time point  $\tau$  (1 month, 12 months, 24 months) are compared, thus disregarding the shape of the survival curves up to time point  $\tau$ . In this analysis the Com-Nougue approach will be applied.

In the Com-Nougue approach the survival proportion at time point  $\tau$  is calculated for both arms.

A 95% Confidence interval and two-sided p-value will be calculated for the Risk Difference, being the difference in these survival proportions, are constructed using the Greenwood Standard Error of the survival proportions, as estimated by KM-analysis. In the calculation the complement of the survival proportions is used, measuring the incidence of the reported event.

No standard SAS procedure is available for this analysis, the analysis is therefore specified in this section.

The Risk Difference (RD) is the difference between the two KM-estimates:

$$(1) \quad RD = KM_{\text{Ivus Guidance}} - KM_{\text{Angio Guidance}}$$

A positive Risk Difference ( $RD > 0$ ) indicates a higher event rate for the Ivus Guidance arm than for the Angio Guidance arm, a negative Risk Difference ( $RD < 0$ ) indicates a lower event rate for the Ivus Guidance arm than for the Angio Guidance arm

The standard error of the Risk Difference is calculated as:

$$(2) \quad SE_{RD} = \sqrt{SE^2_{\text{Ivus Guidance}} + SE^2_{\text{Angio Guidance}}}$$

A 95% confidence interval ( $CI_{RD,95\%}$ ) is calculated for the risk difference by applying the standard normal distribution:

$$(3) \quad CI_{RD,95\%} = [RD - Z_{0.975} * SE_{RD}, RD + Z_{0.975} * SE_{RD}]$$

where  $Z_{0.975}$  is the value of the standard normal distribution which has an upper tail probability of 2.5%, this value is around +1.96.

The p-value for the superiority test is the two-sided p-value for the difference between the Risk Difference in the trial (RD) and the assumed difference under the Null Hypothesis ( $H_0: RD=0$ ):

$$(4) \quad Z_{RD} = (RD - 0) / SE_{RD} = RD / SE_{RD}$$

The two-sided p-value ( $P_{RD}$ ) for superiority is calculated applying the standard normal distribution:

$$(5) \quad P_{RD} = 2 * P(Z > |Z_{RD}|).$$

When reporting the primary endpoint the IVUS guidance strategy is declared superior to the Angio Guidance strategy if the Risk Difference is negative ( $RD < 0$ ) and the two-sided p-value for superiority ( $P_{RD}$ ) is maximum 0.05.

In case Hazard Ratios are reported the Cox proportional hazards model will be applied.

Stratified analyses according to acute coronary syndrome, sex, SYNTAX Score I, distal LM bifurcation and the presence or absence of diabetes will be carried out.

Further details of the statistical methods, analysis and handling of missing data are described in a statistical analysis plan (SAP).

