| Objective                | To assess the superiority of an IVUS-guided approach versus a qualitative angio-guided approach in the setting of left-main PCI.                                                                                                                                                                                                                                                                                                                                                                                                                                                                                                                                                                                                                                                                                                                                       |
| Design                   | The OPTIMAL study is a randomized, controlled, multicentre, international study. A total of 800 participants will be randomized in a 1:1 fashion to IVUS-guided PCI versus qualitative angio-guided PCI, stratified by site. Patients will be consented prior to the PCI procedure and then followed up to 2 years after the index procedure.                                                                                                                                                                                                                                                                                                                                                                                                                                                                                                                          |

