| Clinical sites           | Approximately 30 sites in Europe                                                                                                                                                                                                                                                                                                                                                                                                                                                                                                                                                                                                                                                                                                                                                                                                                                       |
| Investigational strategy | IVUS-guided approach in the setting of left-main PCI                                                                                                                                                                                                                                                                                                                                                                                                                                                                                                                                                                                                                                                                                                                                                                                                                   |

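### The confirmatory 24-month risk-difference test in protocol Section 8.2.1 uses neither site nor recorded baseline predictors: it is valid, but gives up about 1 to 4 points of power under assumed covariate strength

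*Protocol*

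**What the plan says.** Randomisation is 1:1 with site as the only stratification factor. Protocol Section 5.3 gives the reason: "Stratification by site is performed to ensure balance across potential local differences in treatment practices". The Protocol Outline expects "Approximately 30 sites in Europe", so about 800/30 = 27 patients per site.

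Section 8.2.1 writes the primary test out in full, in formulas (1) to (5). The risk difference is the IVUS Kaplan-Meier incidence minus the angiography Kaplan-Meier incidence. Its confidence interval and p-value "are constructed using the Greenwood Standard Error of the survival proportions, as estimated by KM-analysis". Its standard error is the square root of the sum of the two squared arm-level Greenwood standard errors, and the ratio is referred to the standard normal distribution. The rule is that "the IVUS guidance strategy is declared superior to the Angio Guidance strategy if the Risk Difference is negative" and the two-sided p-value is at most 0.05. No site strata, weights or covariates appear.

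This is not left to the SAP. The section states: "No standard SAS procedure is available for this analysis, the analysis is therefore specified in this section". Only further details and missing-data handling are deferred.

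Baseline factors appear in a separate sentence, outside the decision rule: "Stratified analyses according to acute coronary syndrome, sex, SYNTAX Score I, distal LM bifurcation and the presence or absence of diabetes will be carried out". Sections 5.3 and 5.4 show that age, medical history, LVEF and serum creatinine are recorded before PCI, and ACS presentation follows from inclusion criterion 4.

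**The concern.** Formula (2) treats the arms as two independent simple random samples. When allocation is balanced within sites and sites differ in risk, part of the between-site variation no longer contributes to the true variance of the risk difference, yet the arm-level Greenwood errors still count it. Separately, variation in outcome that known predictors could explain stays in the standard error as noise.

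At stake is precision in a trial planned at 80% power. Adjustment for values already being collected costs no recruitment and need not change the quantity estimated. If it is to be part of the confirmatory test it has to be fixed in advance, because adding covariates after outcomes by arm are known would look data-driven.

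**Working it through.** **Inputs from Section 8.3:** 2-year event rates 26% (angiography) and 17% (IVUS); cross-over 4% and 3%; two-sided alpha 0.05; power 80%; 789 participants needed; 800 planned; 6% attrition. **Not in the documents:** between-site variation and the prognostic strength of covariates. Both are assumed below.

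**Step 1. The plan's own figure.** Rates diluted by cross-over:

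- angiography: 0.96 × 0.26 + 0.04 × 0.17 = 0.2564
- IVUS: 0.97 × 0.17 + 0.03 × 0.26 = 0.1727
- difference: 0.0837

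The usual pooled Z-test formula gives 377 per arm, 754 in total. With a continuity correction it gives 400 per arm, 800 in total. Inflating the undiluted requirement by 1/(1 − 0.07)² instead gives 754 uncorrected and 805 corrected. With an exact 35% reduction (16.9%) the corrected totals are 782 and 786. So 789 is matched to within 3%, and only with a continuity correction. All these routes use the unadjusted comparison.

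**Step 2. Power of the planned test.** With n per arm,

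SE = √[(0.2564 × 0.7436 + 0.1727 × 0.8273)/n] = √(0.3335/n), and power = Φ(0.0837/SE − 1.96).

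- 800 patients (n = 400): SE = 0.0289, power 82.6%
- 752 patients (800 × 0.94; n = 376): SE = 0.0298, power 80.2%

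**Step 3. Effect of adjustment.** If the adjustment variables explain a share R² of outcome variance, SE is multiplied by √(1 − R²), and the requirement of 789 by (1 − R²).

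| Assumed R² | SE, 752 | Power, 752 | SE, 800 | Power, 800 | 789 becomes |
|---|---|---|---|---|---|
| 0 | 0.0298 | 80.2% | 0.0289 | 82.6% | 789 |
| 1% | 0.0296 | 80.6% | 0.0287 | 83.0% | 781 |
| 2% | 0.0295 | 81.0% | 0.0286 | 83.4% | 773 |
| 5% | 0.0290 | 82.2% | 0.0282 | 84.5% | 750 |
| 10% | 0.0283 | 84.2% | 0.0274 | 86.3% | 710 |

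The gain runs from 0.4 points (R² 1%) to 4.0 points (R² 10%, at 752).

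**Step 4. Separating site from covariates by simulation.** Set-up: 30 sites, permuted blocks of 4 within site, binary 24-month outcome, 2,000 trials per scenario, and an average unadjusted SE under the alternative of 0.0288 to 0.0289 (the value for 800 patients). The Monte Carlo error of each power figure is about √(0.83 × 0.17/2000) = 0.8 points.

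| Site SD (logit) | Covariate log-odds per SD | Unadjusted | Site | Site + covariate |
|---|---|---|---|---|
| 0 | 0 | 82.7% | 82.4% | 82.2% |
| 0.3 | 0 | 83.0% | 82.8% | 82.8% |
| 0.5 | 0 | 83.4% | 84.2% | 83.9% |
| 0.3 | 0.5 | 83.6% | 83.6% | 84.3% |
| 0.5 | 0.7 | 81.7% | 82.2% | 85.2% |

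Site alone moved power by −0.4 to +0.8 points. Site plus a prognostic covariate moved it by about +1 to +3.5 points.

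A second simulation used 752 patients in 30 unequal sites, 6,000 trials per scenario. Site stratification gave 81.1% against 80.4% at site SD 0.5, and no gain at SD 0.3. A prognostic score with c-statistic 0.66 to 0.70 gave 83.6 to 84.4% against 80.5 to 81.1% unadjusted. A third, also with 752 patients in unequal sites, gave −0.3 to +1 point for site alone and about 1 to 4 points for a covariate.

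**Step 5. Size of the planned test.** Type I error of the unadjusted test was 4.1 to 5.6%, 4.3 to 4.9% and 4.4 to 5.6% in the three simulations. With 2,000 trials the Monte Carlo error is about √(0.05 × 0.95/2000) = 0.5 points, so this is nominal size.

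**Step 6. A site-weighted alternative.** Mantel-Haenszel weighting of site-level Kaplan-Meier differences with per-site Greenwood variances was checked under the null (752 patients, rate 21.5%, no censoring, 20,000 trials per scenario). Type I error was 5.5 to 6.2%, against 4.5 to 5.1% for the planned test. A site-arm without events contributes zero variance. That happened in about 6 to 8% of site-arms with equal sites and 18 to 19% with unequal sites.

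**The case against.** The best defence is that nothing here is an error. The unadjusted test agrees with the Z-test used for planning in Section 8.3. The stated purpose of stratifying by site is balance, which randomisation delivers whatever the analysis does. The test is fully written out and needs no rules for small sites or missing covariates. All of that stands, and it is why this is a point about efficiency only.

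Three further objections stand in part. First, covariate strength is assumed, and the simulations used binary outcomes and linear adjustment for a single score, not a standardised Kaplan-Meier estimate with several measured covariates. The upper end of the gain is therefore a favourable case. Second, LVEF is collected under standard care and may sometimes be missing. Third, ACS and diabetes are not wholly ignored, since separate stratified analyses use them; but those analyses do not enter the decision rule.

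That the SAP might settle the matter does not stand for the primary test: an SAP that adjusted it would contradict Section 8.2.1. It does stand for whether the log-rank and Cox analyses are stratified by site, which is ordinary SAP detail and no finding here.

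**Conclusion.** The primary test is valid but somewhat less precise than the collected data allow. Adjustment for a few baseline predictors would raise power by about 1 to 4 points, from about 80% at 752 patients or 82.6% at 800. Very weak predictors (R² near 1%) would bring less than half a point. Site alone brings about −0.4 to +1 point. That the test is fixed without site or covariates is certain from the text. The size of the gain rests on the assumed covariate strength and site variation.

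Three stronger readings are tempting and are not supported:

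- **That ignoring the stratification factor gives the test the wrong size.** Simulated type I error was nominal, at most slightly conservative where sites and covariates were strongly prognostic.
- **That the site mismatch is itself costly.** With about 27 patients per site its effect is close to nil; nearly all the gain comes from covariates.
- **That the trial has no reserve after 6% attrition.** The 80.2% figure treats 48 patients (800 × 0.06) as contributing nothing. Kaplan-Meier uses them until censoring, and Sections 5.14 and 5.15 keep data up to withdrawal and continue to seek information from other sources. On the plan's rates, power lies between 80.2% and 82.6%.

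**What to change.** Amend Section 8.2.1, and the SAP to match, before any outcome data by arm are seen.

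- Keep the 24-month risk difference as the estimand. Make the primary test a covariate-standardised (g-computation-type) 24-month risk difference that handles censoring, with a robust or bootstrap standard error.
- Adjust for a short fixed list of pre-randomisation values: ACS presentation, diabetes, age, creatinine and LVEF, with a simple stated rule for missing values.
- Include site, with small sites pooled by a rule fixed in advance, for example by country.
- Do not use Mantel-Haenszel weighting with per-site Greenwood variances over unpooled small sites, for the reason in Step 6.
- Do not adjust for SYNTAX Score I unless it is read from pre-PCI images blind to arm. Section 5.12 has it scored from images submitted after the procedure.
- Report formulas (1) to (5) as the unadjusted sensitivity analysis.

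The cost is protocol and SAP wording, modest programming, one pooling rule and one missing-covariate rule. No additional patients or data collection are needed. Checking the chosen estimator's size by simulation at the planned site structure would be prudent, because that exact estimator has not been tested here.
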